**Table 1 Study specific procedures for ARM A**

**1.3 ENDURE-CML: study specific procedures for ARM B (surveillance)**

|                                                                            | Screening
(within
2 months) | Baseline
(day 0) | ARM B (surveillance) |   |   |   |   |   |   |   |     |    |    |    | End-of-
Treatment
3 | Surveillance Phase |    |    |    | Post Study
Follow Up  |
|----------------------------------------------------------------------------|-----------------------------------|---------------------|----------------------|---|---|---|---|---|---|---|-----|----|----|----|---------------------------|--------------------|----|----|----|--------------------------------------|
| Visit Number                                                               |                                   | 1                   | 2                    | 3 | 4 | 5 | 6 | 7 | 8 | 9 | 10  | 11 | 12 | 13 |                           |                    |    |    |    |                                      |
| Months after randomization                                     | -2                                | 0                   | 1                    | 2 | 3 | 4 | 5 | 6 | 7 | 8 | 9,5 | 11 | 13 | 15 |                           | 18                 | 21 | 24 | 25 | 36, 48, 60                           |
| Informed consent                                                           | X                                 |                     |                      |   |   |   |   |   |   |   |     |    |    |    |                           |                    |    |    |    |                                      |
| Inclusion and exclusion criteria                                           | X                                 |                     |                      |   |   |   |   |   |   |   |     |    |    |    |                           |                    |    |    |    |                                      |
| Serologic testing Anti-HIV,
HCV+HBs                                     | X                                 |                     |                      |   |   |   |   |   |   |   |     |    |    |    |                           |                    |    |    |    |                                      |
| Randomization                                                  |                                   | X                   |                      |   |   |   |   |   |   |   |     |    |    |    |                           |                    |    |    |    |                                      |
| Demographic data, Sokal,
EUTOS, EURO, ELTS score                        | X                                 |                     |                      |   |   |   |   |   |   |   |     |    |    |    |                           |                    |    |    |    | X                                    |
| Medical history, pre-treatment
history                                  | X                                 |                     |                      |   |   |   |   |   |   |   |     |    |    |    |                           |                    |    |    |    | X                                    |
| Physical examination / vital
signs / body temperature                   | X                                 | X                   | X                    | X | X | X | X | X | X | X | X   | X  | X  | X  | X                         | X                  | X  | X  | X  |                                      |
| ECOG PS                                                                    | X                                 | X                   | X                    | X | X | X | X | X | X | X | X   | X  | X  | X  | X                         | X                  | X  | X  | X  |                                      |
| Safety laboratory analyses                                     | X                                 |                     | X                    | X | X | X | X | X | X | X | X   | X  | X  | X  | X                         | X                  |    |    |    |                                      |
| Blood Count                                                                |                                   |                     |                      |   |   |   |   |   |   |   |     |    |    |    |                           |                    | X  | X  | X  |                                      |
| BCR-ABL transcripts (IS)                                       | X                                 | X                   | X                    | X | X | X | X | X | X | X | X   | X  | X  | X  | X                         | X                  | X  | X  | X  | X                                    |
| Pregnancy testing                                              | X                                 |                     |                      |   |   |   |   |   |   |   |     |    |    |    |                           |                    |    |    |    |                                      |
| Autoimmunity (ANA, TSH)
screen                                          | X                                 |                     |                      |   |   |   |   |   |   |   |     |    |    | X  |                           |                    |    |    |    |                                      |
| Serum for immune parameters                                                |                                   | X                   |                      |   |   |   |   |   | X |   |     |    |    | X  |                           |                    |    |    |    |                                      |
| Cellular Immune-Marker
(FACS) and stem cell
persistence  |                                   | X                   | X                    |   |   |   |   |   | X |   |     |    |    | X  | X                         |                    |    |    | X  |                                      |
| IFNa prediction scores  (PB)                                   |                                   | X                   | X                    |   |   |   |   |   | X |   |     | X  |    | X  |                           |                    |    |    | X  |                                      |
| TKI intake for 30 days                                                     |                                   | X                   |                      |   |   |   |   |   |   |   |     |    |    |    |                           |                    |    |    |    |                                      |
| Quality of life                                                            |                                   | X                   | X                    | X | X | X | X | X | X | X | X   | X  | X  | X  |                           |                    |    |    | X  |                                      |
| Concomitant treatment                                                      | X                                 | X                   | X                    | X | X | X | X | X | X | X | X   | X  | X  | X  | X                         | X                  | X  | X  | X  |                                      |
| Adverse events                                                             | X                                 | X                   | X                    | X | X | X | X | X | X | X | X   | X  | X  | X  |                           |                    |    |    |    |                                      |

**Table 2 Study specific procedures for ARM B**

ANA = antinuclear antibodies; ECOG PS = Eastern Cooperative Oncology Group performance score; FACS = fluorescence activated cell sorting; IS = international scale; TKI = ABL-specific tyrosine kinase inhibitor (e.g., imatinib, dasatinib, nilotinib)

---

**Legend to table 1a and table 1b**

1. Visits can be pre- or postponed by 7 days.
2. Randomization could be done up to two working days prior to potential study treatment start. If the patient will not meet all the inclusion criteria / fulfill the exclusion criteria, or will withdraw his informed consent before the randomization, he/she must be registered by KKS Marburg using the Screening/Randomization form
3. A pre-mature end of treatment (EOT) assessment must be performed before months 15 for reasons outlined in section 13 and latest at the scheduled next visit. A regular end of treatment visit can be pre- or postponed by 10 days.  
**IMPORTANT:** a premature end of treatment, in case of molecular relapse (loss of MMR) or withdrawal of informed consent, irrespective of whether occurring in arms A or B requires to immediately resume TKI therapy. **After the premature EOT Visit has been performed, a molecular BCR-ABL follow up every three months until month 25 is required.** After month 25 off study follow ups will occur annually, as indicated in the flow chart.
4. Safety laboratory analysis should not be older than 7 days before start of study treatment with AOP2014 in arm A. If the Baseline Visit (V1) will not be performed within 1 week from Screening Visit, the safety laboratory analyses assessments have to be repeated on V1 for arm A. This includes: complete blood counts including differential blood count (machine), Na, K, Ca, Krea, Urea, GOT, GPT, AP, GGT, LDH, Bilirubine, total Protein, PT, PTT, Glucose (see 12.1.2 and 12.2.8).
5. BCR-ABL PCR must be performed at one of the two EUTOS-certified laboratories named in section 12.2.10: 20 – 30 ml blood are required.  
BCR-ABL PCR must have been confirmed three times with at least MR^4 please refer to inclusion criterium number 5.
6. For every visit HCG from serum only in Arm A in women of childbearing potential.  
Additional HCG urine test for home use > 28 days only in Arm A in women of childbearing potential.
7. For immune / stem cell marker 30ml (CD86+pDCs) of heparin and 5ml Serum are required (see 12.2.11). Shipment of samples to Marburg should be performed Monday-Thursday and is possible by regular mail.
8. For interferon alpha (IFN) response and adverse event prediction scores (see 12.2.11), please send 9 to 10 ml EDTA peripheral blood (PB) by regular mail to Aachen.
9. **PSFU:** Patients, who are in TFR 25 months after randomization, are recommended to undergo quantitative BCR-ABL RT-PCR (IS) monitoring every three months. However, an "off study" documentation of molecular remission will be required only once yearly for three years, namely 36, 48 and 60 months after randomization.  
For all patients, the following data will be documented in PSFU:
  - a) Survival (y/n)
  - b) Type of current treatment for CML
  - c) Demographic data including treatment history and relevant medical history (secondary malignancies, cardiac disease, auto-immune disease, progression of CML)
  - d) BCR-ABL RT-PCR (IS)

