**Koordinierungszentrum für klinische Studien (KKS)**

**Philipps-University Marburg**

**[name]**

**D-35043 Marburg**

**Monday-Thursday 8.00–16.00 h**

**Friday 08.00–14.00 h**

**[contact]**

**[contact]**

Randomization will not be possible during public holiday.

The randomization of an eligible patient can take place if all inclusion criteria and none of the exclusion criteria are fulfilled. Therefore the investigator completes the study specific randomization form, which is a part of the Investigator's Folder (ISF), and sends it to KKS Marburg *via* fax. In this form the investigator has to fill in also the Patient-ID (Pat-ID). Pat-ID is combined from the site number (2-digit, starting with 01) and a sequencing number of the patients starting with 001 for each site. This unique Pat-ID is used for all documentation on e-CRF and DCF.

KKS Marburg reports the randomization result back to the center.

The chance for randomization to the investigational arm or the standard arm is 1:1. Permuted block randomization will be used, stratified by:

- site
- prior failure of a TKI discontinuation attempt (yes/no)

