## 7 Blinding

This is an open-label assessor blinded study. Subjects and investigators will be not blinded to the treatment assignment. A placebo-controlled randomization was not considered meaningful, because flu-like side effects regularly occur and would make a blinded, placebo-controlled treatment futile.

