#### 12.1.2 Randomization and Baseline Visit (V1)

##### 12.1.2.1 Randomization

When all of the inclusion criteria and none of the exclusion criteria are met, the randomization of an eligible patient can take place within the Baseline Visit (see 6).

##### 12.1.2.2 Baseline Visit (V1) - Month 1

Time between Screening Visit and Baseline Visit should not exceed 2 months.

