#### The Baseline Visit includes:

- Serum for immune parameters
- FACS and stem cell persistence
- IFNa prediction score
- TKI intake
- AOP2014 dosing and drug accountability (only arm A)
- Physical examination, vital signs and body temperature
- ECOG performance score
- BCR-ABL-PCR test at study reference laboratory in Jena or Mannheim

- Clinical Laboratory Evaluation
- Serum/urine pregnancy test
- Local tolerability assessment (only arm A)
- QoL
- Concomitant medications and AEs

Safety laboratory analysis should not be older than 7 days before start of study treatment with AOP2014 in Arm A. If the Baseline Visit (V1) will not be performed within 1 week from Screening Visit, the safety laboratory analyses assessments have to be repeated on V1 for arm A. This includes: complete blood counts including differential blood count (machine), Na, K, Ca, Krea, Urea, GOT, GPT, AP, GGT, LDH, Bilirubine, total Protein, PT, PTT, Glucose.

At Baseline Visit all of the patient will receive a patient diary. Moreover, patients who were randomized in arm A will be provided with enough pens to last until next scheduled visit.

Female patients are required to have a negative pregnancy test. Additional pregnancy urine tests should be given to woman with childbearing potential in arm A for using at home in case the time between visits exceeds 28 days. The investigator or study nurse has to explain the application of urine pregnancy tests.

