### 12.2.16 Quality of Life Questionnaires

QoL will be assessed with the EORTC Quality of Life Questionnaire (QLQ-C30) version 3, the CML24 module.

QoL questionnaires must be filled out at the hospital/practice when the patient comes for a scheduled visit. The questionnaires will be handed out to the patients by the investigator or a study nurse prior to seeing the doctor for clinical evaluations. Patients will be asked to fill out the questionnaires as completely and accurately as possible. The average time to complete the entire questionnaire is approximately 10-15 minutes. QoL should be assessed at time-points indicated in 12.1 and Table 1 and Table 2.

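### The protocol does not require the only baseline quality-of-life questionnaire to be completed before the open-label allocation is known

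*Protocol*

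**What the plan says.** **When QoL is measured.** Section 12.2.16 states "QoL questionnaires must be filled out at the hospital/practice when the patient comes for a scheduled visit" and "QoL should be assessed at time-points indicated in 12.1 and Table 1 and Table 2". In Tables 1 and 2 the QoL row is empty at Screening and has its first entry at Baseline (day 0). The Screening list in section 12.1.1 does not include QoL; the Baseline list in section 12.1.2.2 does.

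**When randomization happens.** Note 2 of the legend to the schedule tables: "Randomization could be done up to two working days prior to potential study treatment start". Section 12.1.2.1: "the randomization of an eligible patient can take place within the Baseline Visit".

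**Who knows the arm.** Section 7: "Subjects and investigators will be not blinded to the treatment assignment". Section 6: "KKS Marburg reports the randomization result back to the center". When the patient is told is not stated.

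**The only ordering rule for the form.** Section 12.2.16: "The questionnaires will be handed out to the patients by the investigator or a study nurse prior to seeing the doctor for clinical evaluations".

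**The concern.** QoL before and after stopping the TKI is a secondary objective (section 3.2). Section 4.2 plans to compare QoL between the arms, and section 16.5 calls it mandatory and asks for the effect of interferon on it. The Baseline Visit supplies the reference value for these aims.

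The scores are self-reported, and the arms differ visibly: 15 months of self-injected interferon against no drug. A patient who already knows the arm may answer differently, out of relief, disappointment or expectation of side effects. A shift of this kind that differs between the arms would enter any contrast that uses the baseline value.

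The order of data collection cannot be left to an analysis plan, because no later analysis can recover answers given before allocation.

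**Working it through.** The protocol attaches no figure to this point, so the check sets the provisions side by side.

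**Step 1: is there another clean baseline?** No. Screening has no QoL. Visit 2, at month 1, has QoL but comes after randomization, and by then arm A has had a month of AOP2014. The Baseline Visit form is the only one that is both before TKI stop and before study treatment.

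**Step 2: randomization one or two working days before the visit** (note 2). The form is completed at a scheduled visit, and the first visit with QoL is Baseline. Allocation therefore always precedes the form. The centre has the result, the patient is not blinded, and no provision withholds the arm until the form is done.

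**Step 3: randomization within the Baseline Visit** (section 12.1.2.1). The form is handed out before the patient sees the doctor (section 12.2.16), and the investigator completes and faxes the randomization form (section 6). The questionnaire can come first. It need not, because its order is set only against the doctor's clinical evaluations.

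**Step 4: does the schedule expect the arm to be known at this visit?** Yes, for several items:

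| Baseline Visit item | Arm A | Arm B |
|---|---|---|
| Safety laboratory (Tables 1 and 2) | marked | not marked |
| Pregnancy testing (Tables 1 and 2) | marked | not marked |
| First AOP2014 dose, local tolerability, pens | yes | no |

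The arm-specific steps need the allocation before the visit ends. They do not show where the questionnaire falls relative to it.

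**Step 5: which contrasts would be affected?** Let *d*₀ be the difference between arms (A minus B) in the shift of the baseline score caused by knowing the arm, *d*ₜ the same difference at a later visit, and *b* the slope of follow-up on baseline. The awareness component of each contrast is:

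- change from baseline: *d*ₜ − *d*₀
- baseline-adjusted: *d*ₜ − *b·d*₀
- follow-up score alone: *d*ₜ

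Only the terms in *d*₀ come from the order of the baseline form. The documents give no value for *d*₀, *d*ₜ or *b*. If the shift persists unchanged (*d*ₜ = *d*₀), it cancels in the change score. If it fades, −*d*₀ remains. Size and sign are therefore open.

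**The case against.** The strongest reply has three parts.

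- **The order may already be right on the day.** Early randomization is permitted, not required. With same-day randomization, handing the form out before the doctor is seen sits naturally before the investigator faxes the randomization form. This stands in part: it makes a clean baseline possible, but nothing requires it, and it does not help when randomization is done earlier.
- **The harm needs an analysis that the protocol does not name.** Section 16.7 gives descriptive statistics for the secondary endpoints and specifies no change-from-baseline or baseline-adjusted QoL model. A comparison of follow-up scores alone would not use the baseline. This stands, and it limits the severity. It does not remove the point, because the objective of comparing QoL before and after TKI stop needs a before value.
- **Later QoL is open-label self-report anyway.** This is true, and the fix would not change it. It would protect only the reference value.

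A reader might also infer that the baseline is always, or usually, answered with the arm known. The documents do not support that: the order is open on the day, they do not say how often the early option is used, and they do not say when the patient is told.

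**Conclusion.** The point holds as a gap in the order of procedures. The baseline QoL value may be answered with the arm known: allocation certainly comes first under early randomization, and may come first under same-day randomization. Any contrast that uses the baseline could be biased.

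The size of the bias cannot be stated. A reader might assume that knowing the arm moves a 0–100 score by 1 to 3 points in opposite directions, and conclude that change scores are biased by 2 to 6 points (1 + 1 to 3 + 3) at every later visit. The documents give neither the shift nor its direction, and that result also requires the shift to vanish after baseline although patients stay unblinded.

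Severity is low. QoL is a descriptive secondary endpoint outside the four-hypothesis hierarchy of section 16.1. The primary endpoint rests on BCR-ABL measurements from the reference laboratories, and the sample size and type I error do not depend on QoL. The point is still worth acting on because the loss cannot be repaired afterwards and the remedy is simple.

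**What to change.** In sections 12.1.2 and 12.2.16, require the baseline QLQ-C30 and CML24 to be completed before the randomization form is faxed, or at the latest before the patient is told the arm. Record the date and time of completion.

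If randomization is done ahead of the Baseline Visit, either collect the form at the Screening Visit, and add that option to section 12.1.1 and to Tables 1 and 2, or withhold the result from the patient until the form is completed at the Baseline Visit.

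The cost is a change in the order of a questionnaire already planned, with no new instrument and no extra visit. A form moved to Screening may be up to 2 months old at baseline, the longest interval that section 12.1.2.2 allows, and some forms would come from patients who are never randomized. The documents do not show how much a 2-month-old value would lose. Completing the form at the Baseline Visit before disclosure avoids that loss.

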#### **12.1.4 End-of-Treatment assessment Visit 13 (Month 15)**

A regular End-of-Treatment (EOT) assessment will be performed 15 months after randomization in **arms A and B** (procedures are outlined in Table 1 and Table 2).

Patients who relapse or otherwise discontinue the study treatment prematurely, before month 25, will also undergo an EOT visit prematurely; see 12.1.5. This visit should be scheduled closely to the date when the reason leading to treatment discontinuation (see 13) occurred, but latest at the date of the scheduled next visit. The further molecular BCR-ABL RT-PCR (IS) follow up will then be every three months until month 25 (12.1.6). A molecular and demographic/clinical Post Study Follow Up will be once every year for another 3 years (see study flow chart 1.1, Table 1 and Table 2 and 12.1.7).

**IMPORTANTLY:** In case of molecular relapse (loss of MMR) or withdrawal of informed consent TKI treatment must be resumed immediately in **arms A or B**, irrespective of the phase of study.

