#### **12.1.5 Premature End-of-Treatment assessments**

Patients, who relapse **in arm A or arm B**, will resume TKI therapy and perform an early (premature) EOT visit. The molecular BCR-ABL RT-PCR (IS) follow up will then be performed and documented in the e-CRF (every 3 months after resuming the TKI as in surveillance phase until month 25 (see study flow chart 1.1 and Table 1 and Table 2).

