## 13 Discontinuation criteria

### 13.1 Withdrawal of patients from study treatment

All patients have the right to withdraw from the study at any time, for any reason, and without penalty or loss of benefits to which the patient is otherwise entitled. If the patient chooses to withdraw, the investigator must be informed immediately.

In case of premature end of the individual study therapy upon request of the patient, all efforts should be made to keep the patient in the study for follow-up. This is only possible if the subject will be informed verbally on the medically preferred option to still continue with the study surveillance procedures. The patient will then give his/her informed consent by means of a written, signed and dated consent form for the follow-up period. **The study visit(s) will then be continued according to protocol until the regular end of study (intention to treat).**

Reasons to prematurely discontinue study treatment in arm A or treatment free surveillance in comparator arm B **may** also be terminated by the investigator for one of the following reasons:

- Intolerable AEs / side effects of the study medication
- Severe (S)AE which make it necessary to stop study treatment permanently
- Abnormal laboratory value(s) which make it necessary to stop study treatment
- Non-compliance with the study protocol

Study treatment **must be** terminated for one of the following reasons:

- Pregnancy
- Reaching the primary endpoint, which is defined as an increase of the BCR-ABL level to > 0.1% (IS) at any time, corresponding to loss of MMR at any time
- Withdrawal of patient's consent to study treatment
- Study treatment termination by the investigator

**In case of molecular relapse (loss of MMR) or withdrawal of informed consent TKI treatment must be resumed immediately in arms A or B, irrespective of the phase of study.**

If the investigator terminates the treatment of patient prematurely, he has to inform the patient about his decision and has to record the primary reason for withdrawal in the patient file and to document the end of treatment in the e-CRF. Final study evaluations will be done according to the EOT visit. If the patient caused the premature withdrawal, all data before termination may be used for final analysis please also refer to 12.1.5 Premature End-of-Treatment assessments.

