### 16.5 Quality of life assessment

Primary objective:

- determine prospectively QoL of patients after stopping +/- IFN from randomization until EOS. This is a secondary endpoint and therefore mandatory.

Secondary objectives:

- to evaluate the impact of treatment discontinuation of QoL according to treatment arm
- to evaluate the impact of IFN therapy on QoL and to validate the CML24 module

The aim of QoL evaluation in this study is to get a better understanding of the effects of the treatment in terms of frequency and degree of related side effects from the perspective of the patients.

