## 16.10 Sample Size Calculation

Molecular relapse-free survival (RFS) will be tested at three fixed times, 7, 13, and 25 months after randomization. In arm B, without any treatment after stopping TKI, the probabilities of molecular RFS at 7, 13, and 25 months are assumed to be 55%, 50%, and 45%. At each time, an increase by an absolute value of 20% in arm A is expected. At all three times, confirmatory testing is intended. To avoid an inflation of type I error, the hypotheses are put in hierarchical order. At all times, a power of 80% is planned. It is a characteristic of the binomial distribution that the variance is the higher, the nearer the probabilities are to the level of 50%. Accordingly, sample size estimation needs to be based on the assumptions at 25 months.

Patients in the standard arm B are expected to have a molecular relapse-free survival probability of 45% 24 months after discontinuation of TKI treatment. In the investigational arm A, we expect that the molecular RFS probability after 24 months of discontinuation of TKI can be increased by 20% as compared with the standard arm. Accordingly, 192 patients need to be randomized 1:1 to be able to reject the null hypothesis of same relapse-free survival probabilities with a two-sided uncorrected chi-square test at a significance level of 0.05 and a power of 80%. With an expected drop-out of 10%, the 1:1 randomization of 214 patients is necessary. The sample size calculation was performed with the program “PS Power and Sample Size Calculations”, Version 3.1.2 (Dupont WD et al., Controlled Clin Trials, 1997).

The hierarchical ordering of the hypotheses will be in accordance with the chronological ordering of the times. Assuming that all drop-outs will occur before 6 months (the most adverse case), 192 patients would be ready for analysis. With these 192 patients randomized 1:1, a molecular RFS probability of 55% at 7 months in arm B and of 75% in arm A, we would be able to reject the null hypothesis of same relapse-free survival probabilities with a two-sided uncorrected chi-square test at a significance level of 0.05 with a power of 83%.

With 192 patients randomized 1:1, a molecular RFS probability of 50% at 13 months in arm B and of 70% in arm A, we would be able to reject the null hypothesis of same relapse-free survival probabilities with a two-sided uncorrected chi-square test at a significance level of 0.05 with a power of 81%.

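### After a premature end-of-treatment visit the protocol requires only BCR-ABL PCR, so quality of life after relapse and TKI restart is not collected for the planned between-arm comparison

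*Protocol*

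**What the plan says.** **Follow-up after an early stop.** Section 12.1.4 covers relapse and other early stops together: "Patients who relapse or otherwise discontinue the study treatment prematurely, before month 25, will also undergo an EOT visit prematurely". It then continues: "The further molecular BCR-ABL RT-PCR (IS) follow up will then be every three months until month 25". Section 12.1.5 repeats this for relapse: "The molecular BCR-ABL RT-PCR (IS) follow up will then be performed and documented in the e-CRF". Section 12.1.6 does so for relapse in the surveillance phase, and note 3 of the table legend states "a molecular BCR-ABL follow up every three months until month 25 is required". None of these places mentions QoL.

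**When QoL is measured.** Section 12.2.16 ties the questionnaires (EORTC QLQ-C30 and CML24) to the time points in section 12.1 and Tables 1 and 2. The tables mark QoL at Visits 1 to 13, and Visit 13 is the EOT visit.

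**Status of QoL.** Section 16.5 sets the aim: "determine prospectively QoL of patients after stopping +/- IFN from randomization until EOS. This is a secondary endpoint and therefore mandatory". It also asks for the impact of discontinuation by treatment arm. Section 16.4 lists QoL with the secondary efficacy endpoints and plans a comparison between the groups. Section 16.7 assigns those endpoints to the ITT population, by randomized arm.

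**Section 13.1.** When the investigator ends treatment, "Final study evaluations will be done according to the EOT visit". Regular visits go on to the normal end of study in one situation only, an early end that the patient asks for, and only with a new written consent. That rule opens with the words "In case of premature end of the individual study therapy upon request of the patient, all efforts should be made to keep the patient in".

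**The concern.** A site that follows sections 12.1.4 to 12.1.6 and note 3 would stop handing out questionnaires after the premature EOT visit. Relapse is the event behind the primary endpoint and is assumed to differ by 20 percentage points between the arms. Whether a later QoL value exists would therefore depend on outcome and on arm.

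The missing period is the one after relapse and TKI restart. Part of the effect of a discontinuation strategy on QoL arises there. At later visits the observed groups would no longer be the randomized groups, although the protocol plans an ITT comparison. This is a gap in data collection, so an analysis plan cannot close it. Without questionnaires from that period, any estimate for it rests on assumptions that the trial's data cannot test.

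**Working it through.** **Inputs, all from section 16.10.** Molecular RFS in arm B: "at 7, 13, and 25 months are assumed to be 55%, 50%, and 45" percent. Arm A is assumed 20 points higher, so 75%, 70% and 65%. Randomized: 214, so 107 per arm. Expected drop-out: 10%.

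**The plan's own figures.** For 45% versus 65% (mean 55%), two-sided 0.05, power 80%, uncorrected:

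n per arm = [1.960 × √(2 × 0.55 × 0.45) + 0.842 × √(0.45 × 0.55 + 0.65 × 0.35)]² / 0.20² = 95.9, rounded up to 96, so 192 in total.

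192 / 0.90 = 213.3, rounded up to 214. Power with 96 per arm is 0.833 at month 7, 0.812 at month 13 and 0.800 at month 25. The protocol's figures are reproduced.

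**Patients on PCR-only follow-up through relapse.** Expected number per arm = 107 × (1 − RFS), counting every RFS event as a relapse.

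| Month | Arm A | Arm B | Difference | Share of all 214 |
|---|---|---|---|---|
| 7 | 107 × 0.25 = 26.8 | 107 × 0.45 = 48.2 | 21.4 | 35% |
| 13 | 107 × 0.30 = 32.1 | 107 × 0.50 = 53.5 | 21.4 | 40% |
| 25 | 107 × 0.35 = 37.5 | 107 × 0.55 = 58.9 | 21.4 | 45% |

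At month 13 about 75 patients in arm A and 53 to 54 in arm B would still be relapse-free. With 96 per arm after drop-out, the relapse counts are 24 and 43 at month 7, and 29 and 48 at month 13.

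**Does the meaning of end of study matter?** Section 14.2 uses month 15 for arm B, while section 12.1.8 gives 25 months per patient. Of the relapses assumed by month 25, 0.45/0.55 = 82% in arm B and 0.25/0.35 = 71% in arm A have occurred by month 7. The gap is present under either meaning.

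**Other early stops in arm A.** Let s be the share of relapse-free arm A patients who stop AOP2014 early and move to PCR-only follow-up. The arm A share without further QoL is 1 − RFS_A × (1 − s). At month 13, against 50% in arm B:

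- s = 0: 30%
- s = 10%: 1 − 0.70 × 0.90 = 37%
- s = 20%: 1 − 0.70 × 0.80 = 44%
- s = 27%: 1 − 0.70 × 0.73 = 49%

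The shares are equal at s = 1 − RFS_B/RFS_A. This is 1 − 0.55/0.75 = 27% at month 7 and 1 − 0.50/0.70 = 29% at month 13. The protocol gives no value of s for AOP2014. Section 2.2 reports 73% still on treatment at 12 months for a different pegylated interferon given with nilotinib. That makes 27% a possible value, but it is not an estimate for this trial.

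**The case against.** **The protocol never says that QoL stops, and section 16.5 says it continues.** True as far as it goes. However, section 12.2.16 sends the site to section 12.1 and the tables for the time points, and those give none after a premature EOT. The continuation sentence in section 13.1 is written for stops at the patient's request. If full visits were meant for everyone, these sections conflict and need reconciling.

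**The premature EOT visit carries QoL.** This stands. A reader might infer that QoL ends at relapse itself. It does not: there is a record at or shortly after relapse, at the latest at the next scheduled visit. A relapse found at month 7 still yields a questionnaire at about that time, so the month-7 counts somewhat overstate what is missing at month 7 itself.

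**Arm B need not lose far more patients overall.** This also stands. The 20-point gap is from relapse alone, and section 12.1.4 puts other early stops, intolerance in arm A among them, on the same follow-up. The numbers could come close to balance. The missing patients would then be mostly relapsers in arm B and a mixture of relapsers and intolerant patients in arm A. Equal counts would not make the comparison sound.

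**Size of bias.** If relapse with TKI restart shifted a 0–100 score by 5 to 10 points, the month-13 comparison would be off by 0.20 × 5 to 0.20 × 10, that is 1 to 2 points. The protocol supplies no such shift or its direction, so this illustrates scale only.

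**The endpoint is descriptive, and its stated interest is QoL under stopping conditions.** Sections 16.7 and 16.11 place QoL outside the confirmatory tests, and a patient back on a TKI has left the stopped state. That limits the consequence. It does not settle the matter, because section 16.5 also asks for the impact by treatment arm and section 16.7 specifies ITT.

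**Conclusion.** The point holds as a gap in data collection and an internal inconsistency. After a premature EOT for relapse, or for another stop that the patient did not request, the protocol requires three-monthly PCR and no QoL. It nevertheless makes QoL mandatory to the end of study and plans an ITT comparison. On its own RFS assumptions, relapse alone puts about 27 (A) and 48 (B) of 107 patients on PCR-only follow-up by month 7, and 32 and 54 by month 13. The arm difference in total loss is uncertain and disappears if about 27% to 29% of relapse-free arm A patients stop early. Dependence on outcome, and different causes by arm, remain in either case.

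Later QoL comparisons would mainly reflect patients still relapse-free and on their assigned strategy. Two further inferences are not supported. The primary analysis is not weakened, since PCR follow-up continues. Nor does the plan lack an ITT rule for QoL: it has one, but will not have the data to apply it. The change should be made, but it concerns a descriptive secondary endpoint.

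**What to change.** State in sections 12.1.4 to 12.1.6 and in note 3 of the legend that EORTC QLQ-C30 and CML24 continue after any premature EOT, in both arms and whatever the reason, at the follow-up contacts already required. The post-relapse PCRs are timed from TKI restart and need not fall on the QoL months. Align these contacts with the regular QoL months or give them windows, at least up to month 15 and at month 25. Reconcile these sections and section 13.1 with section 16.5, and say which month ends the QoL period. The ITT comparison already planned can then be carried out.

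One query to settle in the same edit: Table 2 marks QoL at month 25, while no mark after month 15 is visible for arm A in Table 1. Table 1 may have been distorted in PDF reading, so this is only a request to confirm.

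The cost is a short amendment and a questionnaire of 10 to 15 minutes (section 12.2.16) at each contact. The downside is a small added burden for patients who have stopped early. No clinical rule needs to change.
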